#### *Proactive outreach*

All participants assigned to the proactive care intervention arm are mailed personalized invitation materials. The invitation packet includes a letter and brochure describing the types of tobacco treatment services available to help MHCP enrollees quit smoking. To help them access the available treatment, the materials include instructions for enrollees interested in discussing their smoking to (a) call a toll free number to speak directly with a smoking cessation counselor or (b) return, in a self-addressed stamped envelope, a reply card with contact information.

Three weeks after the mailed invitation materials are sent (or earlier for participants who respond), participants receive an outreach call from a counselor trained in motivational interviewing and smoking cessation treatment. Up to 6 contact attempts are made at different times of the day (i.e., morning, afternoon, evening) during the week. The purpose of the outreach call is to 1) deliver motivational advice to quit smoking, 2) promote self-efficacy, 3) encourage participants to participate in smoking cessation treatment, and 4) provide information on the safety, efficacy, and functional benefits of pharmacotherapy, particularly NRT. However, both a participant’s willingness to engage in this type of discussion and his or her receptivity to treatment-relevant information is variable. Counselors employ motivational interviewing techniques with consideration for the participants’ current stage of change [25]. For example, the counselor asks, “Can we talk about your smoking behavior to see what services might be best for you now or in the future?” Then the counselor assesses the participant’s readiness to quit smoking using a scale from 0 (“no thought of quitting”) to 10 (“taking action to quit”) [26]. The content for the call is then tailored to the smoker’s readiness to quit, individual concerns about quitting, and the associated SCT factors that must be targeted to promote progression through the stages of change, such as self-efficacy and outcome expectations. Because motivational interviewing uses a patient-centered, autonomy-emphasizing approach, rapport may be more easily established, especially among those not highly motivated to quit. Our findings from focus groups with low-income and minority smokers who had negative experiences with being “told” to quit or “scared” into quitting support this approach [27].

#### *Telephone care*

Telephone care in this study combines free proactive phone-based counseling with free NRT. The telephone counseling protocol is similar to that used by state quitlines. Specifically, we use an adaptation of the evidence-based California Helpline protocol, which uses a combination of motivational interviewing and cognitive-behavioral treatment for substance abuse [28]. This standard telephone counseling protocol consists of 7 calls initiated by the counselor, scheduled in a relapse-sensitive fashion over a 2-month period (pre-quit, quit day, then 3 days, 1 week, 2 weeks, 1 months, and 2 months after the quit date). In the pre-quit session, a major portion of the counseling is spent promoting smokers’ self-efficacy using motivational interviewing. Smokers are asked to identify situations in which it would be most difficult to refrain from smoking and to plan realistic coping strategies. During the follow-up calls, the emphasis is on successful implementation of effective coping strategies and relapse prevention. Given variability in participants’ levels of motivation and success with quitting, counseling calls are individually tailored to the participant’s level of motivation and progress. For example, participants who are thinking about quitting but not ready to set a quit date right away, receive motivational interviewing to enhance their readiness to quit. In addition, participants who relapse to smoking are encouraged to set new quit dates using motivational interviewing and repeat the counseling program. In total, a participant is able to receive up to 14 counseling calls.

#### *Free NRT*

The study also provides a free 8-week course of NRT (patch, gum or lozenge), which is mailed directly to participants in anticipation of their quit date. The protocol is based on the US Public Health Service Guideline recommendations [29,30]. All participants who receive telephone counseling are offered NRT unless they have one of the following contraindications: 1) recent (within 2 weeks) heart attack or severe arrhythmia, 2) unstable angina, 3) pregnancy; or they decline medication. If participants are interested in other smoking cessation medications (e.g., bupropion, varenicline), they are referred to their primary care provider to obtain a prescription. Participants who relapse and attempt to quit again are able to receive an additional 4 weeks of NRT.

### Data collection

Data collection occurs at baseline and at 12 months post-randomization. There are three primary sources of individual level data for this study: 1) MHCP administrative data for both pre- and post-randomization periods, 2) participant questionnaire data from baseline and follow-up surveys, and 3) the intervention database (intervention tracking and process data).

#### *Baseline and follow-up survey procedures*

Surveys, particularly of low-income populations, can be susceptible to a low response rate [31,32]. Non-response reduces the effective sample size and can introduce bias and impair the validity and generalizability of results. Mailed surveys assessing Medicaid program members’ quality of care experiences have yielded response rates ranging from 20-50% [33]. A major advantage, however, of using a mailed survey for MHCP enrollees is that there is a strong incentive for enrollees to keep their addresses current in enrollment databases because many receive supplemental income and monthly checks from the government [31].

For the baseline tobacco use survey, we use established modified-Dillman mailed survey procedures [34]. Up to four mailings are sent to the selected participants over the course of five weeks. The first mailing is a pre-notification letter and a reply postcard to return if they have not smoked a cigarette in the past 30 days. The second mailing includes a $2.00 cash incentive, cover letter, the baseline questionnaire, informed consent information, privacy rights information and a self-addressed, business reply envelope. Seven days later, a reminder/thank you post card is sent to potential participants (3rd mailing). Two weeks after the postcard mailing, a replacement questionnaire packet is sent to those who have not yet responded (4th mailing).

The 12 month follow-up survey for all randomized participants follows similar procedures as the baseline survey except that it did not include a pre-notification letter and additional procedures are incorporated in order to reduce attrition. First, instead of a $2.00 incentive, a larger $10.00 incentive is used with the first mailing to promote retention. Second, the follow-up survey includes phone administration (mixed-mode protocol). Approximately five weeks after the initial mailing, participants who did not respond to the mail protocol are contacted for a telephone interview. At least 10 phone call attempts are made at different times of the day and week. Third, tracking procedures for the follow-up survey to reduce attrition are also employed. Using a mixed-mode approach that involves telephone interviews of participants who do not respond to the mail protocol can increase response rates by an additional 5 to 15% [33]. Another advantage of telephone interviews of mail nonrespondents is improved sample representativeness, which potentially reduces nonresponse bias [35].

### Outcomes

The primary outcome is self-reported six-month prolonged abstinence [21] at one year assessed at the population-level (i.e., smoking abstinence among all smokers, including those who use and those who do not use treatment). A participant who smoked at least once on 7 consecutive days or at least once on 2 consecutive weekends in the six-month period is considered a treatment failure. The primary outcome for both groups is measured from the 12 month follow-up survey. Secondary outcomes include self-reported 7-day point prevalence and 30-day point prevalence, defined as having not smoked a part of a cigarette in the past 7 days and as having not smoked a part of a cigarette in the past 30 days, respectively. Following the Society for Research on Nicotine & Tobacco recommendations, biochemical verification of smoking abstinence has not been performed because of the low misreporting rates in large-scale, population based trials that have limited face-to-face contact with study staff [36].

Additional secondary outcomes include utilization of tobacco cessation treatment during the 12 month follow-up (from any source, including care from outside the study) specifically: 1) initiation of combined intensive behavioral counseling and medication treatment, 2) initiation of intensive behavioral counseling, and 3) initiation of medication treatment. These secondary outcomes are primarily assessed using self-report from the follow-up survey because smokers may seek care from outside the study due to the proactive strategies tested. Initiation of medication treatment is defined as using one or more tobacco dependence medications (e.g., NRT, bupropion or varenicline) in the 12 month follow-up period. Initiation of intensive counseling is defined as the completion of at least one call from a telephone counseling program or making at least one visit to a group or individual smoking cessation program in the 12 month follow-up period. In addition, we will assess tobacco dependence medication utilization by extracting pharmacy claims data from the MHCP claims administrative data and examine the prescription rates of individual medications, number of medications prescribed, and duration of medication use.

### Survey measures: potential moderators and confounders

The following participant demographics are collected in the survey: age, gender, race, ethnicity, marital status, United States birth, size of household, number of children in household, education, annual household income, financial stress, and employment status.

#### *Smoking behavior*

Standard questions from the California Tobacco Survey [37], the CDC Behavioral Risk Factor Surveillance System (BRFSS) [38] are used to collect information regarding smoking history, such as age of smoking initiation, previous quit attempts and prior use of tobacco treatment. The Heaviness of Smoking Index is used to assess nicotine dependence [39].

#### *Physical and mental health*

We used instruments from the Patient Reported Outcomes Measurement Information System (PROMIS) developed by the NIH Roadmap initiative to assess physical functioning (short form and global health status) [40]. To assess mental health, we used the PROMIS instruments for anxiety and depression (PHQ-2). To assess alcohol use we used items from the Behavioral Risk Factor Surveillance System (BRFSS) [38] that assess quantity, frequency, and binge drinking. We also used the EQ-5D, which provides a general measure of health status [41].

### Potential mediators

#### *Provider factors*

The provider factors include participants’ perceptions of their primary care provider’s behavior related to delivery of smoking cessation care, and perceived provider bias and cultural competence. HEDIS tobacco performance measures [42] assess participants’ receipt of smoking cessation advice, counseling and treatment from their primary care provider. We used the Physician Bias and Interpersonal Cultural Competence Measures Scale [43] which consists of 3 questions asking about the participant’s being treated with respect by the doctor, the doctor’s understanding of the participant’s background and values, and the participant’s feeling like the doctor looks down on the participant’s way of life. We also assess participant satisfaction with smoking cessation care from their provider [44].

#### *Cognitive factors*

The cognitive factors examined in this study include motivation to quit, self-efficacy, and attitudes toward NRT. The Contemplation Ladder is used to assess motivation to quit and asks participants to indicate their readiness to quit on a scale from 1 to 10 (e.g., “Think I should quit but not quite ready”) [26]. Self-efficacy to quit is assessed with a global measure [45]. We assess beliefs towards NRT using the 12-item Attitudes Towards Nicotine Replacement Therapy (ANRT-12) scale [46]. This scale asks participants to rate their level of agreement or disagreement on the perceived advantages and disadvantages of using NRT. Participants also indicate their degree of certainty regarding whether or not they intend to use NRT during their next quit attempt.

#### *Social environment*

Characteristics of the patient’s social network assessed in the survey include: subjective norms related to smoking, smoking habits of friends and family, and home smoking rules [37]. We also assess day-to-day perceived discrimination experienced by participants due to any cause, not only on the basis of race, using 9 questions that ask about the frequency of exposure to day-to-day experiences of discrimination such as being treated with less courtesy, less respect, or being harassed [47]. Smoking stigma is assessed using an adapted form of the Mental Health Consumers’ Experience of Stigma Scale [48]. This scale asks how frequently a participant has personally experienced sigma, like being viewed unfavorably, avoided, or treated unfairly, because of their smoking status.

### Sample size and power analysis

The power analysis assumes independent samples in the two groups within strata and considers a type one error rate of 0.05 for analysis of the primary outcome, six-month prolonged abstinence. The goal sample size for this study is N = 2500 (1250 per group), which accounts for a 40% nonresponse rate to the follow-up survey to ensure that we have observed smoking status outcome data on 1500 respondents (750 per group). The anticipated six-month prolonged smoking abstinence rate in the usual care arm is between 2% to 5%. This sample size provides over 85% power to detect intervention effects if the intervention raises abstinence rates by 4% and provides approximately 80% power or greater to detect differences if the intervention raises quit rates by 3.5%. The difference this study is powered to detect is of the same relative order of magnitude as those in prior smoking cessation clinical trials (e.g. odds ratios of 1.5 to 2.0) [49].

### Statistical analyses

The primary analysis uses intent-to-treat methodology. The study design is a randomized complete block design with the blocks (or strata) comprising combinations of the two health care programs (Medicaid vs MinnesotaCare), gender, and three age groups (18–24, 25–34, and 35–64). In the analysis we will use stratified logistic regression methods to model the log odds of abstinence (i.e., 6-month prolonged abstinence) or treatment utilization as an additive function of intervention and the healthcare program/age group strata. This regression model is then used to estimate and test intervention effects.

With our anticipated sample size, random assignment is expected to create two groups that are balanced with respect to observed and unobserved baseline characteristics. However, survey nonresponse may introduce substantive imbalance between the intervention and usual care groups. Furthermore, nonresponse may be directly related to smoking status in a non-ignorable manner. To investigate potential differential non-response bias, the respondents in the two groups will be compared with respect to baseline measures a priori known to be related to smoking cessation and treatment utilization. Balance of the two groups will be tested using simple Mantel-Haenszel [2] tests for categorical variables and appropriate parametric tests (e.g. Blocked Anova F-tests) or nonparametric tests (e.g. Wilcoxon rank-sum test) for continuous variables. A common practice within the smoking cessation research community is to treat non-respondents at follow-up as continuing smokers. This practice is perceived to be a conservative approach but does not, in fact, live up to its reputation [50]. To address potential response bias issues, we will implement a propensity-based imputation methodology and pattern-mixture methods in a sensitivity analysis of the primary analyses described above.

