The study is a two group randomized controlled trial (see Figure 1) and was approved by the Institutional Review Boards at the University of Minnesota and the Minnesota Department of Human Services. The study population is stratified by age group (18–24, 25–34, and 35–64), by gender, and by healthcare program (Medicaid and MinnesotaCare). Stratified program enrollee data is obtained from MHCP administrative databases and a baseline participant screening survey conducted prior to randomization to assess current tobacco use as well as additional baseline information. Survey recruitment from the strata follows the proportions present in the MHCP enrollee population. Individuals reporting current tobacco use (defined as having smoked a cigarette in the past 30 days, even a puff) on the baseline survey with a valid home address, and an adequate proficiency in English to complete study surveys and participate in telephone counseling are randomized with equal likelihood to receive either 1) proactive outreach combined with free nicotine replacement therapy (NRT) and telephone counseling, or 2) usual (reactive) care available from primary care providers and/or existing telephone helpline programs. The target recruitment goal is 2500 current cigarette smokers.

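### The blocks are defined by program, gender and age group, but the stated primary and utilization models name only program and age group; gender should be added (minor)

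*Protocol article*

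**What the plan says.** The Statistical analyses section of the protocol article describes the design as follows: "randomized complete block design with the blocks (or strata) comprising combinations of the two health care programs (Medicaid vs MinnesotaCare), gender, and three age groups". That is 2 x 2 x 3 = 12 blocks. The Study design section lists the same three factors: "The study population is stratified by age group (18–24, 25–34, and 35–64), by gender, and by healthcare program (Medicaid and MinnesotaCare".

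The sentence after the block definition gives the logistic model for the log odds of abstinence or treatment utilization "as an additive function of intervention and the healthcare program/age group strata". Two factors are named, which makes 2 x 3 = 6 cells if they are crossed. The model carries the confirmatory result: "This regression model is then used to estimate and test intervention effects".

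Gender appears elsewhere only in the list of survey demographics, under potential moderators and confounders. No section places it in the primary model or says why it is left out.

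**The concern.** An analysis normally conditions on the factors used to block the randomisation. Here one of three is missing from the stated model, directly after all three were listed. Two things are at stake.

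- **Ambiguity.** One analyst could fit all three factors, following the block definition. Another could fit two, following the model sentence. The model behind the primary test should not be open to choice once the data are in.
- **Balance among respondents.** Blocking balances gender at randomisation only. The plan allows for 40% nonresponse, and its own text expects that nonresponse could unbalance the groups. If response differs by gender and by arm, a model without gender passes that imbalance into the treatment estimate.

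**Working it through.** **1. The plan's own figures.** Inputs from the Sample size and power analysis section: 750 respondents per group, usual care abstinence 2% to 5%, alpha 0.05 (taken as two-sided).

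- Sample size: 1500 / (1 − 0.40) = 2500, as stated.
- Power for a 4-point rise (two proportions, pooled variance): 97.7%, 94.5%, 90.4% and 86.0% at usual care rates of 2%, 3%, 4% and 5%. The stated figure of over 85% reproduces.
- Power for a 3.5-point rise: 94.7%, 89.1%, 83.0% and 77.1%. The last value is the reference for step 3. That it lies a little under the stated 80% is a separate matter.

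**2. Design against model.**

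| Factor | Study design | Block definition | Stated model |
|---|---|---|---|
| Program (2) | yes | yes | yes |
| Age group (3) | yes | yes | yes |
| Gender (2) | yes | yes | not named |

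**3. Effect of omitting gender when it is balanced.** Simulation: 1500 respondents, 1:1 within 12 blocks, logistic Wald test, 3000 runs per setting. Assumptions not in the article: the gender odds ratio (OR) for abstinence, a 60% share of one gender, and equal program and age splits.

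| Gender OR | Power, 5% vs 8.5%: without / with gender | Type I error: without / with gender |
|---|---|---|
| 1.0 | 77.8% / 77.8% | 4.4% / 4.4% |
| 1.5 | 77.5% / 77.5% | 4.7% / 4.7% |
| 2.0 | 77.0% / 77.6% | 4.6% / 4.7% |
| 3.0 | 78.6% / 78.9% | 4.6% / 4.8% |

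The largest power difference before rounding is 77.57 − 77.03 = 0.53 points.

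The treatment log odds ratio also barely moves. Without gender it is ln[(0.085/0.915) / (0.05/0.95)] = 0.568. Solving for the gender-specific rates that average to 5% and 8.5%, with a gender OR of 2 and a 60% share, gives 0.572 conditional on gender. The shift of 0.004 is about 2% of a standard error of roughly 0.21.

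**4. Effect when response differs by gender in one arm (hypothetical).** Assume equal gender shares, no treatment effect, abstinence 3.4% and 6.6% (OR about 2), response 60%/60% in usual care and 70%/50% in the intervention arm.

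- Usual care: (0.30 x 3.4 + 0.30 x 6.6) / 0.60 = 5.00%
- Intervention: (0.35 x 3.4 + 0.25 x 6.6) / 0.60 = 4.73%
- Spurious difference: −0.27 points, or 0.27 / 3.5 = about 8% of the 3.5-point effect

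In general, with 60% response overall and a gender gap g in response in one arm, the shift is (g / 2.4) x (gender difference in abstinence):

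| g | Abstinence differs by 1.6 points | Abstinence differs by 3.2 points |
|---|---|---|
| 10 points | 0.07 | 0.13 |
| 20 points | 0.13 | 0.27 |

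The sign reverses if the gap runs the other way. The shift is zero if the gap is the same in both arms or if gender does not predict abstinence. For scale, the standard error of the difference at 5% is sqrt(2 x 0.05 x 0.95 / 750) = 1.13 points, so the largest value is about a quarter of one standard error.

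**5. How many terms the data support.** Expected events for a 3.5-point rise:

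- 2% vs 5.5%: 750 x 0.02 + 750 x 0.055 = 15 + 41.25 = about 56
- 5% vs 8.5%: 750 x 0.05 + 750 x 0.085 = 37.5 + 63.75 = about 101

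Main effects of the three factors need 6 parameters (intercept, intervention, program, gender, two for age), or 56/6 = 9 to 101/6 = 17 events each. Indicators for all 12 blocks need 13, or 56/13 = 4 to 101/13 = 8 each.

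**The case against.** The phrase may be shorthand. It speaks of strata immediately after the strata were defined with gender included, and this is a condensed article whose full analysis plan is not shown. That is plausible, but the phrase names two factors and leaves out exactly one. The article states the model terms, so this is a conflict in the text and not a detail deferred.

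The stratification might concern sampling only. The Study design section could be read that way, since it links the strata to survey recruitment and then says that smokers "are randomized with equal likelihood to receive either" arm. The Statistical analyses section, however, expressly places gender in the blocks of the randomised design.

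The nonresponse route is not ignored either. The plan compares responding groups at baseline and adds propensity-based imputation and pattern-mixture sensitivity analyses. This stands in part: those steps do not put gender into the primary model, but they do look for the same imbalance. Nor would a gender term address nonresponse that depends on smoking status itself, which is one of the plan's stated worries.

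A reader might infer that the primary test is biased or invalid, or that the trial loses meaningful power. The documents do not support that. With gender balanced, type I error is not inflated and power hardly moves. The 0.27-point shift needs gender-specific abstinence and response rates that the article does not give.

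**Conclusion.** The inconsistency is real: a blocking factor is missing, without a reason, from the stated model for the primary and the utilization outcomes. It is minor. For assumed gender odds ratios up to 3, power differs by under 1 point and type I error is 4.4% to 4.8% either way. No sample size or power figure changes. Under one-sided differential response, the shift is about 0.07 to 0.27 points across the assumed range, at most about a quarter of a standard error.

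The gain from correcting it is an analysis that matches the design, a primary model with one reading, and adjustment for any gender imbalance among respondents.

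**What to change.** In the Statistical analyses section, reword the model sentence so that the log odds are *additive in intervention, health care program, gender and age group (main effects)*, and state that this holds for both the abstinence and the treatment utilization models. If gender is left out on purpose, give the reason instead.

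Main effects are safer than 12 block indicators, given about 56 to 101 expected events. The cost is one phrase and one extra parameter. Gender is a stratifier, so it should already be on file for every randomised participant.
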